## Abstract

**Background:**

Venous thromboembolism (VTE) is a common postoperative complication. The perioperative incidence of VTE in patients undergoing neurosurgery on VTE chemoprophylaxis is consistently between 1.7% and 3.5%, excluding patients with trauma. While the majority of VTEs are asymptomatic, symptomatic VTEs may result in serious adverse events or death. There are limited neurosurgery society guidelines making VTE prophylaxis recommendations for patients undergoing cranial or spine neurosurgery. Several societies have published VTE prophylaxis guidelines for neurosurgery, but inconsistent recommendations have led to varied practices based on neurosurgeon preference.

**Objective:**

This study aims to assess whether implementing a single protocol of VTE guidelines at a large hospital system department of neurosurgery would decrease the rate of VTE incidence by 50% within a 12-month period.

**Methods:**

This project uses a department-wide protocol of chemical prophylaxis for admitted patients after neurological surgery. This quality improvement (QI) project has been designed and reported in accordance with the SQUIRE 2.0 (Standards for Quality Improvement Reporting Excellence) guidelines. SQUIRE is the most appropriate framework for reporting system-level interventions aimed at improving health care quality, safety, and outcomes. This manuscript addresses all relevant SQUIRE elements. The primary outcome is the VTE incidence over 12 months following protocol implementation. Secondary outcomes include the incidence of pulmonary embolism, length of hospital stay, and unexpected treatment of patients, such as therapeutic anticoagulation, thrombolysis, or emergency surgical or catheter-directed embolectomy. Balancing measures and process measures are also considered. Interim analyses with department reports will be performed every 3 months, but every VTE event will trigger an analysis of the variables described in this protocol. Analyses will consider barriers to change and adequacy of the protocol to guide protocol modifications and continuous implementation of improvements.

**Results:**

This QI project was approved on February 16, 2023 (protocol ID NEU20230216-01). Adaptation and training began on August 1, 2023. As of May 2024, data collection is ongoing and scheduled to conclude by December 2024. Final data analysis is anticipated in March 2025, with results submitted for publication by the end of 2025.

**Conclusions:**

It is anticipated that this QI project implementing a department-wide protocol for chemical prophylaxis in patients undergoing neurosurgery will improve the rates of VTE in patients on our service. In addition to a discussion of our results, we provide a comprehensive review of the literature and establish a gap in consistent published guidelines for VTE prophylaxis in patients undergoing neurosurgery. Results from this QI project will provide evidence for the effectiveness of a unified protocol of VTE prophylaxis in this patient group. Furthermore, outcomes from this study may be used as the basis for guideline recommendations and will benefit not only our department but may be used for QI of patient care at other hospitals.

**International Registered Report Identifier (IRRID):**

DERR1-10.2196/57278

## Introduction

### Overview

Venous thromboembolism (VTE) is a common postoperative complication. The incidence of VTE in perioperative patients undergoing neurosurgery is consistently between 1.7% and 3.5%, even among patients on pharmacologic prophylaxis, chemoprophylaxis (cPpx), excluding trauma patients [1,2]. A 2015 American College of Surgery (ACS) National Surgical Quality Improvement Program (NSQIP) retrospective analysis [3] of 10,477 patients who underwent cranial surgery across the United States reported an incidence of VTE of 3%-3.4%. Similarly, a single hospital system (Mayo Clinic) analysis of 1622 craniotomies for tumor resections between 2012 and 2017 documented a 3% incidence of VTE [4]. A large retrospective hospital system study (at the University of California) reported the incidence of VTE in patients who underwent spine surgery for nonmalignant versus malignant pathology as 0.5% versus 2.0%, respectively [5]. Incidence of VTE among patients with trauma is, however, much higher. In patients with neurosurgical trauma, the American Association for the Surgery of Trauma (AAST, 2021) cites 20%-30% VTE incidence for traumatic brain injury (TBI) [6,7], while the ACS Best Practices (2022) cites 40%-70% incidence for patients with spinal cord injury (SCI) [8]. As per the North American Spine Society’s (NASS) most recent guidelines on antithrombotic therapies in spine surgery, there exists no high-quality study to establish definitively the incidence of VTE in nonelective spine surgery [5,9]. Most published studies assessing VTE incidence are retrospective analyses of NSQIP or other large hospital system data.

In addition, currently there are no published neurosurgery society guidelines making VTE prophylaxis recommendations for patients undergoing cranial or spine neurological surgery, including the Congress of Neurological Surgeons (CNS), American Association of Neurological Surgeons (AANS), or NASS. Multiple non-neurosurgical societies have commented and made a variety of recommendations for the prophylaxis of VTE in patients undergoing neurosurgical procedures. The American Society of Hematology 2019 Guidelines suggest against routine cPpx in patients undergoing neurosurgery in general but suggest all patients should receive mechanical prophylaxis (mPpx) [10]. They highlight that cPpx should be considered in patients at the highest risk, such as patients experiencing prolonged immobility or those undergoing a major neurosurgical procedure and suggest low molecular weight heparin (LMWH) over low-dose unfractionated heparin (UFH). Similarly, the American College of Chest Physicians (ACCP) 9th Edition Guidelines 2012 suggest mPpx with sequential compression device (SCD) over UFH, LMWH, or no prophylaxis for patients undergoing cranial or spine surgery, and cPpx for patients with very high risk of VTE (ie, malignant disease) once hemostasis is obtained and risk of bleeding decreases [11,12]. The ACCP guidelines recommend against an inferior vena cava (IVC) filter use for primary VTE prevention [13]. The new ACCP 2022 revised guidelines do not mention specific anticoagulation for patients undergoing neurosurgical procedures [12]. For patients with central nervous system trauma, including TBI, SCI, and so on, the AAST VTE Ppx in the intensive care unit (ICU) 2021 Guidelines suggest prophylaxis within 24-72 hours of admission pending stability head computed tomography based on Berne-Norwood criteria [14] with either Enoxaparin 30 mg every 12 hours (with Xa target of 0.2-0.4 mg/mL) or UFH 5000 U every 8 hours [7] (Multimedia Appendix 1).

Moreover, most guidelines do not comment on patients with a BMI>30 kg/m^2^ and do not include this patient population as a confounder in analyses. Based on our summary of the literature, the most frequently used and recommended methods of VTE prophylaxis include the following:

mPpx with sequential compressive devices, which are demonstrated to reduce the risk of deep vein thrombosis (DVT) compared with control treatment (odds ratio [OR] 0.85, 95% CI 0.5-1.50); however, this is based on low-quality evidence [15]. According to a recent Cochrane review, mPpx reduces the incidence of DVT (relative rate [RR] 0.43, 95% CI 0.25-0.73), but cPpx is more effective than mPpx at reducing the incidence of DVT (RR 0.48, 95% CI 0.25-0.95) [16].Chemical prophylaxis with LMWH is considered to reduce the risk of DVT compared to UFH (RR 0.68, 95% CI 0.50-0.94) [15,17]. Patients who received both mPpx and cPpx with LMWH had a lower risk of DVT [16,18]. UFH alone has shown a strong reduction in VTE incidence compared to placebo (RR 0.27, 95% CI 0.10-0.73) [19,20].IVC filter is an alternative prophylaxis for patients at high risk of bleeding in whom cPpx has either been shown ineffective or is contraindicated. Patients receiving an IVC filter had lower incidence of subsequent pulmonary embolism (PE; OR 0.5, 95% CI 1.17-2.48), nonsignificant lower PE–related mortality (OR 0.51, 95% CI 0.25-1.05), and no change in all-cause mortality (OR 0.91, 95% CI 0.70-1.19) [21].

While the majority of VTEs are asymptomatic, symptomatic VTEs may result in serious adverse events or death [4]. Therefore, prophylaxis of VTE plays a major role in reducing adverse events and unexpected mortality in patients undergoing neurosurgery. An ACS NSQIP data query for Ochsner Department of Neurosurgery performed on August 1, 2022, for the period of July 1, 2020, to June 30, 2021, yielded incidence rates of VTE as follows: a total of 8 events per 320 total neurosurgery cases for a rate of 2.5%, whereas the predicted rate of VTE was calculated to be 2.83% and the expected rate based on the national average rate of VTE was calculated to be 3.27%. This has resulted in an OR calculation of 0.86 (95% CI 0.52-1.42). When stratified by the type of neurosurgery, the VTE incidence rate was 0.76%, where a VTE event occurred in 1 case out of a total of 132 spine neurosurgery cases. The predicted rate for spine neurosurgery was 1.78% and the expected rate for spine neurosurgery cases was 2.24%, with an OR of 0.77 (95% CI 0.37-1.61). The rate of VTE after neurosurgery for brain tumors at Ochsner was 3.52%, based on 5 cases out of 142 total brain tumor neurosurgery cases. The predicted rate of VTE incidence for patients undergoing neurosurgery for brain tumor was 3.45% and its expected rate was 3.42%, with an OR of VTE incidence among patients after brain tumor neurosurgery of 1.01 (95% CI 0.63-1.63).

Although the incidence of VTE at Ochsner Health Department of Neurosurgery is within the expected range of nationwide data [1-3], the lack of a department- or hospital-based protocol for postoperative VTE prophylaxis results in a heterogeneity of patient care and may contribute to unexpected outcomes. Current practice dictates that individual physicians apply their chosen set of VTE prophylaxis guidelines [17]. This further contributes to a heterogeneity of patient care since most guidelines provide inconsistent recommendations (Multimedia Appendix 1). This creates a gap in patient care that could potentially be bridged through a consistent set of department VTE prevention guidelines, which would aim to diminish patient care variability and reduce the incidence of VTE below the national average rates.

### Objective

A department-wide protocol will aim to decrease the rate of VTE by providing a set of consistent guidelines for physicians, physicians-in-training, advanced practice providers, and other clinical staff involved in direct patient care. The objective of this quality improvement (QI) project is to assess the effect of implementing a practice-wide protocol of VTE prophylaxis on the incidence of VTE at Ochsner Health among admitted patients undergoing nonemergent neurosurgery procedures. Implementing a department-wide VTE prophylaxis protocol based on individualized patient risk aims to ensure patient-centered care and enhance the safety and effectiveness of postoperative care. Moreover, we propose that establishing consistent guidelines for VTE prophylaxis in postoperative patients will contribute to efficiency and minimize errors based on heterogeneity of care. A further step to improve patient-centered care is the consideration of both patients’ BMI and weight when determining cPpx dosing–a rarely applied approach that is particularly germane for our patient population in the southern United States.

## Methods

### Overview

This project is well aligned with the Institute of Medicine’s 6 domains of quality health care and was designed according to the Institute for Healthcare Improvement steps to a good QI project [22]. It aims to avoid harm to patients while being effective in providing prophylaxis according to a risk-based approach. Specifically, the adaptive design assessing outcomes and process measures and implementing incremental change on a quarterly basis ensure the safety of this QI project. Our protocol follows the Agency for Healthcare Research 2017 guidelines to ensure patient safety while implementing this protocol [23]. This quality improvement project has been designed and reported in accordance with the SQUIRE 2.0 (Standards for Quality Improvement Reporting Excellence) guidelines. SQUIRE is the most appropriate framework for reporting system-level interventions aimed at improving health care quality, safety, and outcomes. This manuscript addresses all relevant SQUIRE elements [24]. Further, this project is patient-centered and aims to ensure equitable care for patients by consistently including all eligible individuals in the protocol without discriminating based on demographics. Finally, it is a timely and efficient protocol, reducing inconsistent application of variable guidelines and thus potentially avoiding supplies and staff waste. The assessment of the impact of this protocol on VTE incidence is at 12 and 24 months post implementation, with interim analyses every 3 months to ensure continuous quality improvement. The goal is a 50% decrease in the overall VTE incidence in patients undergoing neurosurgery from 2.5% to 1.25%, with a greater decrease in incidence of VTE among patients undergoing neurosurgical procedures for malignant pathology (cranial or spine). Targeting a reduction to 1.25% represents an achievable improvement that aligns with outcomes seen in successful QI initiatives with standardized protocols [25-27]. For example, the Mercy Hospital Springfield Neurosurgery VTE quality improvement initiative found that VTE occurrence rates in neurosurgery decreased from 3.97% at the time of protocol initiation to 0.72% in January 2020 [26]. All patients admitted to the neurosurgery service for postoperative care will be managed according to the new protocol after the implementation date. The incidence of VTE among patients admitted during the previous 12 months will serve as a control.

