
Continuous improvement is built with small incremental changes, using a systematic scientific approach to test their impact and feasibility. The Plan-Do-Study-Act cycle will be used as a model on which to structure tests of change. This includes continuous analysis of errors and successes of the protocol and subsequent protocol adaptation for the duration of the project. Dynamic data will be assessed through a run chart with data points added monthly, but with interim analysis every 3 months. Interim analyses will be discussed before changing the protocol for such quality improvement adaptations. A formal statistical analysis will be performed with a *t* test comparing NSQIP and postprotocol end-of-study VTE rates at both 12 and 24 months post implementation. Stratification based on malignancy and cranial versus spine procedures will also be assessed, as will be the confounding process and balancing measures.

Missing data will be handled through checking at each interim review. Any record missing critical outcome or key covariate information will be excluded from regression analyses. In addition, we will conduct sensitivity analyses to assess the impact of any missing data on VTE rates. Discrepancies will be resolved by consensus and reported, if indicated. Interim analyses with department reports will be performed every 3 months, but every VTE event will trigger an analysis of the variables described in this protocol. Analyses will consider barriers to change and adequacy of the protocol to guide protocol modifications and continuous implementation of improvements.

Additional guidance has been incorporated to inform future iterations of the protocol, including considerations for patients with comorbid atrial fibrillation or those already on antiplatelet therapy [34]. Implemented changes will be made based on recent evidence in the literature [35].

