## Results

The desired timeframe for implementing the Neurosurgery VTE prophylaxis protocol is within 6 months of QI project approval, with 1 month of “adaptation time.” Adaptation time is defined as the time between training the staff involved in the project and starting the timeline for outcomes assessment. Department project approval occurred on February 16, 2023, and the project adaptation time began on August 1, 2023.

Data collection is scheduled for completion in 2024, with analysis expected by March 2025. We anticipate a 50% reduction in VTE incidence (from 2.5% to 1.25%) following implementation of a standardized department-wide cPpx protocol. The primary outcome is the incidence of VTE. To assess whether implementation of the protocol results in a meaningful improvement compared to the standard of care, we will use a pre-post design comparing outcomes in the 12 months before and 12 months after the protocol implementation. We will evaluate differences in VTE rates using chi-square or Fisher exact test to compare the proportion of VTE events pre-implementation versus post-implementation. The justification for the chi-square test is that it is appropriate for large samples with expected counts ≥5. The Fisher exact test will be used as a backup for smaller subgroup comparisons where expected frequencies are low. In order to mitigate confounding, we will use multivariable logistic regression, using VTE occurrence as the dependent variable, with covariates including patient-level and procedural risk factors such as BMI, malignancy, surgery type (cranial vs spine), and immobility. The justification is that regression modeling will help isolate any independent effects of the protocol on VTE rates. To account for continuous secondary outcomes, we will perform stratified subgroup analyses for patients with malignancy, those undergoing cranial versus spine procedures, and those receiving LMWH versus UFH. The justification for this is that we will protect against or identify subgroups that experience differential VTE risk. A stratified analysis will determine if the protocol is equally effective across populations.

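### The 24-month analysis is not provided for in the stated schedule: data collection ends by December 2024, when at most 13 to 17 months have passed since implementation

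*Protocol article*

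**What the plan says.** **Time points.** Methods, Overview, states: "The assessment of the impact of this protocol on VTE incidence is at 12 and 24 months post implementation". Methods, Selecting Change, goes further and plans a formal statistical analysis "comparing NSQIP and postprotocol end-of-study VTE rates at both 12 and 24 months post implementation". Only Selecting Change calls the analysis formal; the Overview speaks of assessment.

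**Schedule.** The Abstract's Results say that "data collection is ongoing and scheduled to conclude by December 2024" and that "Final data analysis is anticipated in March 2025". The main Results section agrees: "Data collection is scheduled for completion in 2024, with analysis expected by March 2025". The only later date in the article is submission for publication by the end of 2025.

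**Primary window.** The Abstract's Objective asks whether the protocol "would decrease the rate of VTE incidence by 50% within a 12-month period". The Abstract's Methods define the primary outcome over 12 months after implementation, and the Results section compares 12 months before with 12 months after.

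**Start of the clock.** The Abstract's Results and the main Results section put the beginning of adaptation at August 1, 2023. The Results section allows one month of adaptation and starts outcome assessment after it. Selecting Change puts staff training in September and October 2023.

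**The concern.** The article promises analyses at two time points, but its dates leave room for only one. An analyst following the plan in March 2025 would face month 24 still in the future and data collection already closed. The plan does not say whether to omit the second analysis, run it on whatever has accrued, or wait for data that no section schedules.

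The choice should not be left open, because quarterly interim results will have been reviewed by then and events are few. The baseline is 8 VTEs in 320 cases, and the 1.25% target on a similar volume (an assumption) is 0.0125 × 320 = 4 events. At such counts, one or two events on either side of an improvised cut-off visibly move a rate. A reader of the eventual report could also not tell whether a missing 24-month result was planned, postponed or dropped.

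**Working it through.** This is calendar arithmetic. No power or sample-size formula applies.

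**Inputs**
- Latest reading of data close: December 31, 2024 (Abstract, Results; Results).
- Latest reading of final analysis: March 31, 2025 (same places).
- Stated start of adaptation: August 1, 2023 (same places).
- Adaptation period: 1 month (Results).
- Training: September to October 2023 (Methods, Selecting Change).
- Project approval: February 16, 2023 (Abstract, Results; Results).

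**Formulas**
- Month 24 = start + 24 months.
- Data available = months from start to December 31, 2024.
- Shortfall = 24 − data available.
- Gap after final analysis = months from March 31, 2025 to month 24.

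| Start of clock | Month 12 | Month 24 | Data available | Shortfall | Gap after final analysis |
|---|---|---|---|---|---|
| Aug 1, 2023 (stated start of adaptation) | Aug 1, 2024 | Aug 1, 2025 | 5 + 12 = 17 | 24 − 17 = 7 | 4 |
| Sep 1, 2023 (plus 1 month of adaptation) | Sep 1, 2024 | Sep 1, 2025 | 4 + 12 = 16 | 24 − 16 = 8 | 5 |
| Nov 1, 2023 (after training; inferred) | Nov 1, 2024 | Nov 1, 2025 | 2 + 12 = 14 | 24 − 14 = 10 | 7 |
| Dec 1, 2023 (after training plus 1 month; inferred) | Dec 1, 2024 | Dec 1, 2025 | 1 + 12 = 13 | 24 − 13 = 11 | 8 |

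All durations are in months. Reading the close as December 1, 2024 takes one month off each figure for data available, giving 12 to 16. Month 12 still falls on or before that date in every row.

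**Check that does not depend on the start date.** For 24 months to be complete by December 31, 2024, the clock would have to start by about January 1, 2023. That is before the project existed: "This QI project was approved on February 16, 2023". Counting from approval itself, which is not implementation, month 24 is February 16, 2025, about 1.5 months after the close.

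**The case against.** The strongest reply is that the 24-month analysis is unscheduled rather than impossible. Ethical Considerations describes the data as retrospective chart data, and the Overview places all postoperative admissions under the protocol from implementation with no end date. A later extraction would need no new enrolment. On this reading, the December 2024 and March 2025 dates belong to the 12-month result, and the date for the 24-month result was simply not given. Submission by the end of 2025 could even leave time for it under the earlier starts.

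Part of this stands. A reader might infer that the analysis cannot be done at all, and the article does not support that: extending the dates would make it possible. But the article does not say that the dates apply only to the 12-month result. It calls the March 2025 analysis final, and Selecting Change describes the 12- and 24-month rates alike as end-of-study rates. The late-2025 date concerns submission only and adds no data collection.

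A second reply also stands. The 12-month primary window is already fixed in the Abstract's Objective and Methods and in the Results section, and a 24-month follow-up beside it would be compatible. The conflict is with the calendar, not with the primary definition.

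A reader might also infer that two time points give two chances to declare success. The support for that is weak. The success criterion in the Results section (at least a 50% reduction, from 2.5% to 1.25% or less) names no time point, which leaves some ambiguity. But the Abstract's Objective ties the 50% goal to 12 months, and nothing says that success at either point would suffice.

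**Conclusion.** The point holds as an internal inconsistency of dates. Selecting Change plans a formal 24-month analysis and the Overview a 24-month assessment, while the stated schedule closes data collection with at most 13 to 17 months accrued. Month 24 falls 7 to 11 months after data close and 4 to 8 months after the final analysis.

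The favourable ends of these ranges (17 months of data, a 7-month shortfall) rest on the stated date of August 1, 2023. The other ends (13 and 11 months) rest on an inference from the training dates and the one-month adaptation period. The conclusion is the same for every start considered.

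The consequence is limited. The 12-month primary comparison is feasible throughout, and nothing here casts doubt on it. The plan should still be corrected, because it promises a formal analysis that its own dates do not provide for.

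**What to change.** Reconcile the sections in two steps.

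1. State that the 12-month comparison defined in the Abstract's Objective and Methods and in the Results section is the sole basis for the success criterion in the Results section.
2. Then choose one of the following:
   - Delete the 24-month time point from Methods, Overview, and Methods, Selecting Change; or
   - Keep it as a separate secondary sustainability analysis, with its own data-close and analysis dates after month 24. Name the start date from which month 24 is counted, and revise the schedule in the Abstract's Results and the main Results section to match. Depending on that start, data would have to run to at least August 1 to December 1, 2025.

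Either option resolves the contradiction. The first costs only wording. The second costs wording plus one later routine data extraction.

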Outcomes of this QI project will be reported to the Ochsner Health Department of Neurosurgery as well as hospital administration. Results will also be shared with the scientific and health care quality improvement community. Consideration of “lessons learned” and suggestions for implementing change in order to improve patient outcomes will be made. In addition, consideration of barriers to change and recommendations for improving patient care will be discussed. This project will provide an evidence base for the implementation of the proposed protocol, and its success or failure to achieve the protocol's aims will be equally important for future hospital patient care quality improvement efforts. Considering there are limited neurosurgical society guidelines on VTE prophylaxis in perioperative patients, results from this project can be used to assess the efficacy of our specific protocol in guiding future guidelines specific for patients undergoing neurosurgery. The overarching objective of this quality improvement initiative is to advance the evidence of the effectiveness of anticoagulation prophylaxis in preventing perioperative VTE morbidity and mortality. As previously identified, the determination of whether implementation of this protocol was a success compared to the current standard-of-care success criteria will be measured against a ≥50% reduction in VTE incidence compared to baseline (from 2.5% to ≤1.25%). Secondary success measures include reduction in symptomatic PE and DVT events, and improvement in protocol adherence across clinical teams.

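### The goal of a greater VTE decrease in surgery for malignant pathology has no baseline for its own population, and the planned stratified analyses do not test it

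*Protocol article*

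**What the plan says.** The article describes the tumor or malignancy group in three places, and not in the same way.

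- **Baseline data (Introduction, Overview).** The NSQIP query for July 2020 to June 2021 gives a brain tumor rate "based on 5 cases out of 142 total brain tumor neurosurgery cases". For spine, "a VTE event occurred in 1 case out of a total of 132 spine neurosurgery cases". Neither group is split by malignancy.
- **Goal (Methods, Overview).** After the overall 50% target comes the subgroup goal, "with a greater decrease in incidence of VTE among patients undergoing neurosurgical procedures for malignant pathology (cranial or spine". This group is defined by the reason for surgery and includes spine. It has no baseline rate and no target rate.
- **Analysis (Methods, Selecting Change, and Results).** Selecting Change specifies a test of NSQIP against post-protocol rates and continues: "Stratification based on malignancy and cranial versus spine procedures will also be assessed". Results specifies a comparison of the 12 months before with the 12 months after implementation, and states: "we will perform stratified subgroup analyses for patients with malignancy, those undergoing cranial versus spine procedures". It expects this stratified analysis to settle whether the protocol works equally well across populations.

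Methods, Outcomes names two benchmarks, 2.5% and 3.27%. Neither is for malignancy.

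**The concern.** Malignancy is the only subgroup with a stated direction of effect, so readers will look for a result on it. That result needs the same kind of patient before and after, and a comparison of the two decreases. The article secures neither.

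The brain tumor group may include benign tumors and leaves out malignant spine disease. The goal's group excludes benign tumors and includes malignant spine disease. Patients with malignancy, read literally, also covers someone with cancer who is operated on for a non-malignant condition. Because Selecting Change puts the malignancy strata next to the NSQIP test, an analyst could take the one tumor-related NSQIP rate on the page as the baseline. Part of any apparent change would then reflect case definition rather than the protocol.

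Separately, a decrease in the malignant stratum and a smaller or non-significant one elsewhere would not show that the first is greater. That needs a direct estimate of the difference between them.

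**Working it through.** **1. The article's own rates (Introduction, Overview).**
- Overall: 8/320 = 2.50% (exact 95% CI 1.09% to 4.87%).
- Brain tumor: 5/142 = 3.52% (1.15% to 8.03%).
- Spine: 1/132 = 0.76% (0.02% to 4.15%).

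All three reproduce. If the two strata do not overlap, 320 − 132 − 142 = 46 cases and 8 − 1 − 5 = 2 events lie in neither. Brain tumor is therefore not a stand-in for cranial: if all 46 were cranial, the cranial rate would be (5 + 2)/(142 + 46) = 7/188 = 3.72%.

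**2. Baseline for the goal's population.** It cannot be computed, because neither the 142 nor the 132 is split by malignancy. As an illustration, assume that 50% to 90% of the brain tumor cases (71 to 128) and 5% to 20% of the spine cases (7 to 26) are malignant, that brain tumor events fall in proportion to share, and that 0 or 1 spine event falls in the malignant group.
- Lowest: 2.5 events in 71 + 26 = 97 cases, or 2.58%.
- Highest: (2.5 + 1) events in 71 + 7 = 78 cases, or 4.49%.

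The range lies on both sides of 3.52%. Allowing any allocation of the 6 known events, it runs from 0% to 6/78 = 7.7%.

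The risk ratio matters too. Take brain tumors alone, half of them malignant, with malignant risk r times benign. The malignant rate is r × 3.52%/(0.5r + 0.5), which is 4.7% for r = 2 and 5.6% for r = 4. The 4 is borrowed from the 2.0% versus 0.5% that the Introduction cites for spine surgery. Adding malignant spine cases at a lower rate pulls the figure back down.

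**3. What a mismatched baseline would do.** Let the true relative decrease be d and the correct baseline B. Read against 3.52%, the apparent decrease is 1 − (1 − d) × B/3.52%. I take the goal to mean a decrease above the overall 50%; the values of d are illustrative.

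| True decrease d | Apparent, B = 2.58% | Apparent, B = 4.49% |
|---|---|---|
| 40% (misses the goal) | 1 − 0.6 × 2.58/3.52 = 56% | 1 − 0.6 × 4.49/3.52 = 24% |
| 60% (meets the goal) | 1 − 0.4 × 2.58/3.52 = 71% | 1 − 0.4 × 4.49/3.52 = 49% |

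A failure can look like success and a success can look like failure. The direction depends on a case mix that the article does not give.

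**4. How precisely a greater decrease could be estimated.** Use brain tumor (5/142) and all other cases (3/178) as rough stand-ins for the two strata, with equal numbers afterwards and events halved in both (2.5 and 1.5). The standard error of the log ratio of odds ratios is

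√(1/5 + 1/137 + 1/2.5 + 1/139.5 + 1/3 + 1/175 + 1/1.5 + 1/176.5) = √1.626 = 1.275.

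The 95% interval is the estimate divided and multiplied by exp(1.96 × 1.275), about 12. On these numbers the data could not tell a much greater decrease from a much smaller one.

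**The case against.** The strongest reply is that no section uses 3.52% as the malignancy baseline. It appears once, as background. The named benchmarks are 2.5% and 3.27%, and both Methods, Overview and Results name the preceding 12 months as the control. Data come from charts and malignancy is already a regression covariate, so one definition could be applied to both periods. All of this stands. A reader might infer that the goal is judged against the brain tumor rate, but the document does not say so. The only opening is the wording in Selecting Change.

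A reader might also infer that the mismatch would hide a true benefit. That does not follow: dropping benign tumors and adding malignant spine cases can pull in opposite directions.

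Nor does the success rule in Results contradict the goal by leaving malignancy out. A subgroup aim with no numeric target need not be a success criterion.

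Finally, patients with malignancy may be shorthand, and a condensed article may leave operational definitions to a fuller document. That is fair for the coding detail. It does not remove the differences between the descriptions that the article does state, or supply a baseline for its one directional subgroup goal. Nor does it make separate stratum results a test of a greater decrease.

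**Conclusion.** The point holds as a minor one about a secondary goal. As written, the aim of a greater decrease in surgery for malignant pathology has no baseline for its own patients, and the NSQIP strata beside which it would be assessed do not match it. The stratified analyses in Results would not establish a greater decrease even with a correct baseline.

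If the brain tumor rate were used, the bias could go either way. Its size rests wholly on assumed malignant shares, event allocation and risk ratios, so the ranges above are illustrations and not estimates. Under the 12-month control the baseline mismatch disappears once one definition is applied to both periods. The overall 2.5% to 1.25% comparison is not touched.

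**What to change.** - Use one definition, surgery for malignant pathology (cranial or spine), in Methods, Overview, in Selecting Change and in Results.
- Code it identically from charts in the 12-month control period and the post period.
- State that the NSQIP brain tumor rate is neither the malignancy baseline nor the cranial baseline.
- Assess the greater decrease by the protocol-by-malignancy interaction in the planned logistic model, reported as a ratio of odds ratios with a 95% CI and labelled exploratory.

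The cost is wording, plus consistent coding of a variable already planned as a covariate. The downside is a very wide interval: the only tumor stratum shown had 5 baseline events, so the malignancy result will be descriptive.
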